## **4.3 EXCLUSION CRITERIA**

- Pregnancy
- History of malignancy within the past 2 years
- Confirmed aetiology of the nodule at the time of qualifying CT scan – As this is a diagnostic study, should the aetiology of the nodule be confirmed by investigation such as FDG-PET/CT or bronchoscopy prior to consent the patient remains eligible as the intention to include is made on the analysis of the qualifying CT scan.
- Biopsy of nodule before DCE-CT scan
- Contra-indication to potential radiotherapy or surgery
- Contra indication to scans (assessed by local practice)

All patients meeting inclusion criteria and none of the exclusion criteria will be eligible and recruited consecutively into the study. In giving consent they will be expected to follow the procedures described below

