## **4.2 INCLUSION CRITERIA**

- A soft tissue solitary dominant pulmonary nodule of  $\geq 8\text{mm}$  and  $\leq 30\text{mm}$  on axial plane
  - Measured on lung window using conventional CT scan
  - No other ancillary evidence strongly indicative of malignancy (e.g. distant metastases or unequivocal local invasion)
- If clinicians and reporting radiologists believe the patient is being treated as having a single pulmonary nodule and there are other small lesions  $<4\text{mm}$  that would normally be disregarded, the patient should be included in the trial.
- Nodules already under surveillance can be included provided they have a recent or scheduled FDG-PET/CT
- 18 years of age or over at time of providing consent
- Able and willing to consent to the study.

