## 5 STUDY PROCEDURES

Sites will register patients into the SPUtNik study by sending a signed registration form by Fax or email attachment to SCTU (numbers listed at front of protocol). Sites will be given a block of SPUtNik codes. Sites will allocate trial ID codes consecutively following consent. On registration SCTU staff will check eligibility and confirm the patient study number by email. Both registration and the DCE-CT scan must not take place before informed consent is signed, however registration with SCTU may take place before or after the DCE-CT scan, as some clinics may schedule the DCE-CT scan outside of office hours.

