#### Quantitative analysis

Scans will be analysed and interpreted by PET-CT specialists at each centre.

Quantitative analysis of FDG-PET/CT data will consist of measurements of FDG uptake expressed as the maximum standardised uptake value (SUVmax).

The presence of incidental extra-thoracic findings on PET and maximal tumour diameter as measured by CT will be recorded.

The diagnostic performance of FDG-PET will be assessed with and without incorporation of the CT appearances using the guidelines in table 1 (secondary aim 1).

Based on previous studies [19, 20], the combined FDG-PET/CT assessment will be classified as positive for malignancy if one of the following criteria are met;

- grade 4 on FDG-PET,
- At least grade 3 on both modalities
- Grade 2 on PET and grade 3 or 4 on CT.

| Grade | Significance                 | FDG-PET                      | Attenuation Correction CT                                   |
|--------------|-------------------------------------|--------------------------------------------------|--------------------------------------------------------------------|
| 0            | No evidence of malignancy           | No visible uptake                                | Round, well defined lesion with laminated or popcorn calcification |
| 1            | Low probability of malignancy       | Uptake less than mediastinal blood pool          | Inflammatory features e.g. air bronchograms, enfolded lung         |
| 2            | Indeterminate                       | Uptake comparable to mediastinal blood pool      | Smooth well defined margins, uniform density                       |
| 3            | High probability of malignancy      | Uptake greater than mediastinal blood pool       | Lobulated, spiculated or irregular margins                         |
| 4            | Very high probability of malignancy | Evidence of distant metastases (i.e. M1 disease) | Evidence of distant metastases (i.e. M1 disease)                   |

Table 1: Guidelines for the interpretation of FDG-PET and Conventional CT

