## **8.2 ASSESSMENT OF DIAGNOSTIC ACCURACY OF DCE-CT:**

DCE-CT will be performed immediately after or within a maximum of 21 days either side of the clinically indicated PET/CT examination. Please note scans should ideally be performed within 14 days .

Interpretation of DCE-CT will comprise quantitative analysis performed by specialists at each participating site with central review for quality assurance. Quantitative analysis of DCE-CT data will consist of measurements of contrast enhancement.

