| Reconstruction interval                                     | 2.0 mm or similar depending on scanner                                                              |
| Image time relative to onset of contrast material injection | Pre- contrast, 60s, 120s, 180s and 240s                                                             |
| Reconstruction algorithm                                    | To be specified for each scanner model. Iterative reconstruction (if available) to be switched off. |

*Table 2: Minimum image data set for DCE-CT.*

Patient weight and volume of contrast injected must be recorded accurately.

For each time point, measurements of tumour attenuation (expressed as HU) will be determined in the axial plane from regions of interest with diameters approximately 70% of the nodule's long- and short- axis diameters viewed on mediastinal windows. Maximal nodule enhancement is determined by subtracting the baseline attenuation from each subsequent attenuation value.

DCE-CT scans will be analysed and interpreted by specialists at each centre.

All DCE-CT reconstructed scan images will be transferred to Papworth Hospital where 10% will be second read for audit.

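### Both index tests are read locally with no stated masking or reading order, so either may be read knowing the other test or a prior diagnostic result

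*Protocol*

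**What the plan says.** **Eligibility.** Section 4.3 excludes nodules whose cause was confirmed at the qualifying CT. If it is settled later, by an investigation such as PET/CT or bronchoscopy, "prior to consent the patient remains eligible as the intention to include is made on the analysis of the qualifying CT scan". The same list also excludes "Biopsy of nodule before DCE-CT scan". Section 4.2 adds: "Nodules already under surveillance can be included provided they have a recent or scheduled FDG-PET/CT".

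**Order.** Section 5 states: "Both registration and the DCE-CT scan must not take place before informed consent is signed". On the same day, PET/CT comes first (section 5.1 and Appendix 2). On separate days either scan may come first, up to 21 days apart.

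**Readers.** For PET, section 8.1 says: "Scans will be analysed and interpreted by PET-CT specialists at each centre". For DCE-CT, section 8.2 says: "Interpretation of DCE-CT will comprise quantitative analysis performed by specialists at each participating site with central review for quality assurance". Appendix 3 repeats the point: "DCE-CT scans will be analysed and interpreted by specialists at each centre". Central reading is a second read of 10% of scans of each type, for audit (section 8.1 and Appendix 3), and is not the analysed reading.

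**What is read.** PET and the attenuation-correction CT are each graded on a five-point scale (section 8.1, Table 1), and SUVmax is measured. DCE-CT yields attenuation in HU from regions of interest of about 70% of the nodule's diameters (Appendix 3).

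The protocol nowhere says whether a reader is masked to the other index test, to bronchoscopy or to the final diagnosis, or that one reading must be fixed before another result is opened.

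**The concern.** A reader who knows the other test's result, or that the diagnosis has been settled, may resolve a borderline grade or place a region of interest in line with that knowledge. Masking acts at the moment of reading. An analysis plan written later can describe the exposure but cannot restore independence.

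The comparative aims have most to lose. The incremental-value aim needs a PET grade fixed independently of the CT grade. The joint-strategy aim depends on discordance between PET and DCE-CT: its projected loss of sensitivity consists of cancers that are PET-positive and DCE-CT-negative. If knowledge of PET removes some of that discordance, a real loss looks smaller.

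**Working it through.** **1. The plan's own precision figures.** Section 9.1 uses 375 patients at 68.5% prevalence: 375 × 0.685 = 256.9 malignant and 375 × 0.315 = 118.1 benign. The half-width is 1.96 × √(p(1−p)/n), with n = 257 for sensitivity and 118 for specificity. It gives 4.11 and 6.78 points for DCE-CT (87%/83%) and 3.32 and 5.41 for PET (92%/90%). All four match the plan. They measure sampling error only.

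**2. Who is exposed, and to what.**
- *Finding available before consent.* DCE-CT follows consent, so in these patients it is acquired and read after the finding exists. The biopsy exclusion narrows the group to nodules settled by PET/CT, by bronchoscopy without nodule biopsy, or by similar means.
- *DCE-CT exposed to PET.* This can affect any patient in whom PET comes first, including every same-day patient. Appendix 3 has the nodule checked on the attenuation-correction CT before DCE-CT, and section 1.2 keeps both tests' images and reports in the patient record. The route is mainly region-of-interest placement.
- *PET and CT grades exposed.* This arises where DCE-CT or bronchoscopy came first, or where the PET and CT grades are not fixed separately. If PET itself settled the cause, that knowledge cannot have biased the PET reading.

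**3. Possible size, on assumed inputs.** Let c be the share of would-be errors corrected by knowledge, in all patients. Observed accuracy is p + (1−p) × c, so the shift is (1−p) × c. The last column is half-width ÷ (1−p).

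| Measure | c = 10% | c = 20% | c = 30% | Planned half-width | c needed to reach it |
|---|---|---|---|---|---|
| DCE-CT sensitivity 87% | 1.3 | 2.6 | 3.9 | 4.1 | 32% |
| DCE-CT specificity 83% | 1.7 | 3.4 | 5.1 | 6.8 | 40% |
| PET sensitivity 92% | 0.8 | 1.6 | 2.4 | 3.3 | 41% |
| PET specificity 90% | 1.0 | 2.0 | 3.0 | 5.4 | 54% |

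If only a share f of patients is exposed and a share g of their errors is corrected, c = f × g. With f = 10% and g = 50% (assumed), c = 5% and the shifts are 0.65, 0.85, 0.40 and 0.50 points, in the table's order.

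**4. Joint strategy.** Section 9.1 requires 197 malignant cases (288 in total) to detect a fall in sensitivity from 0.92 to 0.88. With g now the ratio of joint to PET sensitivity, the paired relative-sensitivity formula is n = (1.960 + 0.842)² × [((g+1) × 0.92 − 2 × joint)/(g × 0.92²)]/(ln g)². For joint = 0.88 it gives 196.3, so 197, and 197/0.685 = 287.6, so 288. This reproduces the plan at a two-sided 5% level.

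The 4 points are the PET-positive, DCE-CT-negative cancers. Suppose knowledge of PET turned a quarter of these DCE-CT-positive (assumed). Joint sensitivity would read 0.89, the requirement would be 262 malignant cases, and power at 257 would fall from 89% to 79%. With a half turned (assumed), joint would read 0.90, the requirement would be 393 and power 62%.

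**The case against.** The strongest reply has four parts.

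- *Few diagnoses can be known in advance.* Nodule biopsy before DCE-CT is excluded, and PET/CT is an index test, whereas the reference standard in section 8.4 is pathology and/or 24-month imaging. This stands. A reader might infer that many patients enter with a known diagnosis, but the protocol gives no number and its own exclusion limits the group.
- *DCE-CT is a measurement.* It yields HU values to which thresholds are applied in the analysis, and PET also has SUVmax. This limits the reader's influence without removing it, since placement of the region is the local reader's. It also means that the error-correction model in the working is only an illustration.
- *The direction is not certain.* Knowing the other test pulls a reading towards that test, including when it is wrong. This stands: accuracy need not rise, although concordance would.
- *Informed reading is NHS practice.* The objective is performance in the NHS, where PET readers see clinical information. This has some force for PET. It has less for DCE-CT, because section 8.7 models DCE-CT alone and DCE-CT as the selector for PET/CT, and in both the PET result would not yet exist.

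A reader might also infer that the protocol makes its readers unmasked. It does not say so; it is silent.

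**Conclusion.** The point holds in a limited form. Following the protocol as written allows each index test to be read with knowledge of the other, or of an earlier diagnostic finding. A later analysis plan cannot undo this, so it should be settled in the protocol.

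The size is unknown. On the assumption that 10% to 30% of would-be errors in all patients are corrected, shifts run from 0.8 to 5.1 points, and less if only some patients are exposed. A reader might infer that such shifts reach the planned precision. Across that range none reaches its own half-width; that would need about 32% to 54% of errors corrected. Their importance is that they are systematic and lie outside what the confidence intervals measure. The joint-strategy comparison is the most sensitive, because its target difference is only 4 points.

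Nor do the documents show equal inflation of both tests: PET is often read first and is then less exposed. Keeping patients eligible on the basis of the qualifying CT is not itself a fault.

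**What to change.** - For scans read after enrolment, require the PET grade, then the CT grade, and the DCE-CT region-of-interest values to be entered and locked in the eCRF before the reader opens the other test's result or any pathology or bronchoscopy result. Record at each reading what was already known.
- For PET reported before entry, which an eCRF lock cannot govern, use the report as issued and record its date.
- Carry out the planned 10% central second reads masked to the other test and to all diagnostic results.
- Add a sensitivity analysis that leaves out patients whose aetiology was known before DCE-CT, and report how many there were.

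Eligibility is unchanged. The cost is an eCRF entry-order rule, a field for what was known and one further analysis, with no extra readers. At small sites one specialist may read both scans. Masking will be incomplete there, and this must be recorded.

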#### **Scans:**

- F-DG-PET/CT performed in line with procedure described in Appendix 2
- DCE-CT performed in line with procedure described in Appendix 3

If both scans are performed on the same day F-DG-PET/CT should be performed first with no waiting time required between scans. If scans are performed on separate days either scan can be performed first provided that patient consent and registration takes place before the DCE-CT scan (e.g. in the case of a delay in F-DG-PET/CT).

F-DG-PET/CT and DCE- CT scans will ideally be performed within 14 days – however, an absolute maximum of 21 days is allowed between scans should sites have difficulty with scheduling.

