## **7 DEFINITION OF END OF TRIAL**

This is a non-CTIMP study with all eligible patients recruited consecutively into the study and undergoing each study procedure. Recruitment will be terminated once 375 patients have been recruited and undergone a DCE-CT scan.

The study has two possible endpoints for each patient:

**Either** the diagnosis of lung cancer via biopsy **or** a diagnosis of benign or non- lung cancer via either biopsy (please note that in this case economic data collection will continue to be required for 2 years follow up)

**Or** failure of the imaged nodule to progress (increase in size) during the 2 year follow up period.

The end of the study will be reached when the last study patient reaches two years of follow up or withdraws full consent for continuing in the study.

**PLEASE NOTE:** *Health Resource Data will be collected for all patients over a 2 year period following the DCE-CT scan, therefore the end of study form will not be completed until this time unless patients have withdrawn full consent.*

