## 8.6 SYSTEMATIC REVIEW, META-ANALYSIS AND ECONOMICS ASSESSMENT

The primary outcome measures from the prospective observational study (described in section 3.1) are the diagnostic accuracy (sensitivity and specificity) for  $^{18}\text{F}$ FDG-PET/CT and DCE-CT in relation to subsequent clinical diagnosis of lung cancer. Since test results drive clinical management, patients with positive and negative imaging results are anticipated to face different care pathways and different outcomes (depending on whether their condition was correctly or incorrectly characterised). The systematic review and economic evaluation are intended to extend the analysis beyond an assessment of diagnostic accuracy to encompass the clinical utility and cost effectiveness of alternative strategies for diagnosing malignancy in people with solitary pulmonary nodules of greater than 8mm. This will be done in parallel to the current study and the outcomes will inform the development of the economic evaluation and be presented in the final report, through publication in peer review journals and at conferences. The systematic review process will be supported by an expert advisory group that includes relevant clinicians (e.g. chest physician, radiologist) and academics (e.g. methodologists).

Details of the systematic review protocol will be registered with PROSPERO database and can be found in Appendix 5.

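### Excluding nodules biopsied before DCE-CT can make entry depend on the PET result and so bias PET accuracy, by an amount the protocol gives no means to measure

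*Protocol*

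**What the plan says.** Section 4.3 lists "Biopsy of nodule before DCE-CT scan" as an exclusion, and the synopsis carries the same rule. The preceding criterion, on confirmed aetiology, takes a different line: "should the aetiology of the nodule be confirmed by investigation such as FDG-PET/CT or bronchoscopy prior to consent the patient remains eligible", because inclusion is decided on the qualifying CT.

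On timing, section 4.1 books DCE-CT for the day of PET/CT or within 14 days, and section 5.1 adds that "an absolute maximum of 21 days is allowed between scans should sites have difficulty with scheduling". Section 5.1 also states: "If scans are performed on separate days either scan can be performed first provided that patient consent and registration takes place before the DCE-CT scan". PET may come before enrolment: section 4.2 says "Nodules already under surveillance can be included provided they have a recent or scheduled FDG-PET/CT".

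On what follows a result, section 8.6 says: "Since test results drive clinical management, patients with positive and negative imaging results are anticipated to face different care pathways and different outcomes". On numbers, section 7 says: "Recruitment will be terminated once 375 patients have been recruited and undergone a DCE-CT scan".

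**The concern.** The biopsy exclusion stays open until DCE-CT, so it can act after one of the two index tests has been read. Suppose a patient has PET first, the report is positive, and biopsy is done before DCE-CT. That patient becomes ineligible. A patient with a negative PET who goes to surveillance remains. Entry then depends on the PET result, and because only patients who have had DCE-CT count towards the 375, each lost patient is replaced by one who passed the filter.

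The first primary objective is a high-precision estimate of the accuracy of both tests. A selection bias does not shrink as the sample grows. The accuracy estimates feed the economic model, and section 9.1 bases one set of predictive values on the study prevalence, which would also shift. Section 8.4 already accepts the principle: it argues that requiring a clinically indicated biopsy for entry would make the sample unrepresentative. The same reasoning applies to excluding on an early biopsy, but the protocol does not discuss it.

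Separately, a bronchoscopic biopsy before consent falls under two bullets of section 4.3 that point in opposite directions.

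**Working it through.** **Inputs from section 9.1.** N = 375; prevalence 68.5%; about 257 malignant and 118 benign nodules; PET sensitivity (Se) 92% ± 3.3 points; PET specificity (Sp) 90% ± 5.4 points.

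**Input not in the documents.** The share of nodules biopsied before DCE-CT: *f* among PET-positive and *g* among PET-negative nodules. Both are assumed below and, unless stated, are the same for malignant and benign nodules.

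**Step 1: the plan's own precision.** Half-width = 1.96 × √[p(1 − p)/n].
- Sensitivity: 1.96 × √(0.92 × 0.08/257) = 3.32 points.
- Specificity: 1.96 × √(0.90 × 0.10/118) = 5.41 points.

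Both agree with the protocol.

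**Step 2: values after selection.**
- Se′ = Se(1 − f) / [Se(1 − f) + (1 − Se)(1 − g)]
- Sp′ = Sp(1 − g) / [Sp(1 − g) + (1 − Sp)(1 − f)]
- With g = 0, prevalence′ = 0.685(1 − 0.92f) / [0.685(1 − 0.92f) + 0.315(1 − 0.10f)]

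Example, f = 20%, g = 0: Se′ = 0.736/(0.736 + 0.08) = 90.2%; Sp′ = 0.90/(0.90 + 0.08) = 91.8%.

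| f (g = 0, assumed) | Sensitivity | Specificity | Prevalence | Share of all patients lost |
|---|---|---|---|---|
| 0% | 92.0% | 90.0% | 68.5% | 0% |
| 5% | 91.6% | 90.5% | 67.6% | 3.3% |
| 10% | 91.2% | 90.9% | 66.6% | 6.6% |
| 20% | 90.2% | 91.8% | 64.4% | 13.2% |
| 30% | 89.0% | 92.8% | 61.9% | 19.9% |

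**Step 3: how the result depends on the assumptions.**
- Some PET-negative nodules are also biopsied early (g = f/4, f = 20%): 90.6% and 91.4%.
- Biopsy is unrelated to PET (g = f): 92.0% and 90.0%, so no bias.
- Only PET-positive cancers are lost, no benign nodules (f = 20%): sensitivity 90.2%, specificity unchanged at 90.0%.

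**Step 4: when the bias equals the planned half-width.**
- Sensitivity falls to 88.7% when 0.92(1 − f) = 0.887 × 0.08/0.113 = 0.628, so f is about 32%.
- Specificity rises to 95.4% when 0.10(1 − f) = 0.90/0.954 − 0.90 = 0.0434, so f is about 57%.

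**The case against.** The strongest reply is that the route is narrow. It needs PET first, on a separate day, with the report acted on and the biopsy done before DCE-CT. Same-day scanning is the first arrangement described, 14 days is the usual limit, and 21 days is a ceiling for scheduling difficulty. DCE-CT may come first, which closes the route. Section 5.2 places management, including biopsy, after both scans. Section 11.3 foresees a biopsy on the day of PET, but that biopsy was booked before the PET result, is expected to be rare, and is met by shortening the consent interval to keep the patient. All of this stands. It makes the bias conditional, and *f* may be small: at 5% sensitivity moves by 0.4 points.

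A reader might also infer that PET data from a consented patient biopsied between the scans are discarded. The protocol does not say so. Section 5.5 continues data collection for patients who withdraw from a scan only, section 5.3 collects outcomes when DCE-CT is aborted for an invisible nodule, section 9.1 analyses each test in its own right, and section 7 is a recruitment stopping rule rather than an analysis-set definition. What remains is that none of these provisions names the patient biopsied between scans, whom section 4.3 makes ineligible.

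Nor does the clause "the patient remains eligible as the intention to include is made on the analysis of the qualifying CT scan" fix all eligibility at the qualifying CT. It explains one criterion, and section 4.3 then requires that no exclusion applies. The two bullets can be read cumulatively, but their overlap for bronchoscopic biopsy still needs a clear answer.

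Finally, requiring both tests in the same patients is a legitimate choice for the paired comparison. It is not a reason to leave a completed PET result and reference standard out of the PET estimate.

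**Conclusion.** The point holds as a possible bias that the rule leaves open, not as one shown to occur. If PET-positive nodules are biopsied before DCE-CT more often than PET-negative ones, PET sensitivity and study prevalence are biased down. A reader might infer that losing PET-positive cancers also raises specificity. It cannot, because cancers are not in the denominator of specificity; PET-positive benign nodules must be lost too.

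The size is unknown from the documents. Under the assumed range of 5% to 30% of PET-positive nodules lost, no PET-negative nodules lost, and equal loss in malignant and benign nodules, sensitivity falls by 0.4 to 3.0 points and specificity rises by 0.5 to 2.8 points. Throughout that range the bias stays inside the planned half-widths, but at the upper end it takes up most of the 3.3 points allowed for sensitivity. This is a cheap improvement to a stated rule, not a flaw that undermines the design.

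**What to change.** 1. Keep in the study every consented patient biopsied between PET and DCE-CT. Use the PET result and the reference standard in the PET accuracy analysis, and record DCE-CT as not done because of biopsy.
2. Log otherwise eligible patients biopsied between PET and consent. Limiting the exclusion to biopsies before consent would not be enough alone, because a recent PET can precede consent.
3. Report PET accuracy with and without the patients biopsied between the scans, and in patients consented before the PET report was available.
4. Reconcile, in section 4.3 and the synopsis, the biopsy exclusion with the sentence on aetiology confirmed by bronchoscopy, so that a bronchoscopic biopsy falls under one rule.

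**Cost.** Revised eligibility wording, dates for biopsy and for the PET report, a short log and supplementary analyses. No extra scans and no change in care. The PET and paired analysis sets will differ slightly in size. Because section 7 counts only patients who have had DCE-CT, the paired sample is not reduced. The fix does not recover DCE-CT results for these patients, but the log shows how many there were and how their PET results were distributed.
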